# 1. Introduction

## 1.1. Background

Human macula has yellow pigment called macular pigment that consists of three carotenoids, lutein ((3R,3’R,6’R)-lutein), zeaxanthin ((3R,3’R)-zeaxanthin), and *meso*-zeaxanthin ((3R,3’S;*meso*)-zeaxanthin).(Fig. 1)

[figure not shown]
Fig.1 Structure of lutein and zeaxanthin

Humans are not able to synthesize lutein and zeaxanthin, and they are obtained from dietary sources such as green leafy vegetables and as supplements. Hydrophobic lutein and zeaxanthin are absorbed into the small intestine in the micellarized forms, and they are uptaken by the retinal pigment epithelial cells from the choroiocapillaris and stored in the inner plexiform layers of the retina. The uptake and accumulation of lutein and zeaxanthin in the retina is affected by many factors. Several receptor proteins participate in the absorption of lutein and zeaxanthin to be in the intestine and in their transport into the retina. Scavenger receptor class B type 1 (SR-B1) participates not only in the uptake of lutein and zeaxanthin absorption in the intestine, but it is also involved in the process in their transport from the choriocapillaris to the retinal pigment epithelium (RPE). Interphotoreceptor retinoid binding protein (IRBP) may work as a transporter from the RPE cells to the outer segment of the photoreceptor cells. Within the retina, lutein and zeaxanthin deposit specifically via their respective specific binding proteins (pi isoform of glutathione S-transferase (GSTP1) for lutein, steroidogenic acute regulatory domain 3(StARD3) for zeaxanthin. *Meso*-zeaxanthin is not contained in the foods and it is thought to be mostly converted from lutein in the retina.

Recently, researchers are studying the relation between the macular pigment and age-related macular degeneration (AMD). AMD is a leading cause of legal blindness in aged people in the US and Europe, and the number of patients with AMD is increasing even in Asian countries. AMD is divided into two types, atrophic AMD and exudative AMD. There is no effective therapy to atrophic AMD. Photodynamic therapy and intravitreous injection of anti-VEGF agents have been developed for the treatment of exudative AMD, but these treatments do not cure AMD and the treatment has to be repeated for years. Patients with AMD suffer from central scotoma and dismorphopsia and visual disturbance reduces the quality of life. AMD is a multifactorial disorder and genetic factors, aging, and various environmental factors are involved in its onset. Recently, the oxidant stress in the retina caused by the external light is attracting the attention as one of the environmental factors. External light is absorbed by the visual pigment in the photoreceptor cells to create the visual perception, and activates intraretinal oxygen and lipofuscin to produce singlet oxygen and radicals which cause oxidation of the photoreceptor cell membrane and injury of photoreceptor cells. Macular pigment absorbs blue light and acts as a filter that might attenuate photochemical damage on the retina from blue light. It also works as an antioxidant that may protect against light-induced oxidative damage in the retina by quenching oxygen radicals. These light protection effects of macular pigment have been expected to prevent AMD.

On the other hand, macular pigment has some effects on visual functions. The relationship between macular pigment and visual functions have been investigated and several reports suggested the improvement of contrast sensitivity, glare sensitivity and other functions such as photostress recovery and visual discomfort, although some studies failed to show the effectiveness.

We have reported in our previous studies that macular pigment optical density (MPOD) decreases with age, MPOD is lower in men than women, MPOD of the eyes with AMD is lower than healthy eyes and even the patient’s fellow eye free from AMD has lower MPOD than healthy eyes. We also revealed that MPOD and serum concentration of lutein increased under lutein intake (10 mg/day) in the persons not having AMD but did not in some patients with AMD. In these previous studies, we used FlorGLO as lutein supplements. The particle size of lutein affects bioabvailability. Generally, small size of lutein particle is thought to be solved into lipid and micellarized more efficiently than large size of particle, and high efficacy of micellarization of ingested carotenoids in the intestine had a marked effect on the extent to which the compounds are absorbed**.**

In the current study, we compared the efficacy to increase MPOD levels and plasma lutein concentration in normal, healthy Japanese subjects between two lutein supplements; one was FloraGLO lutein (Kemin Japan, Tokyo, Japan) that was supposed to be most widely used in the world and the other was Xanmax lutein (Katra Phytocem, Bangalore, India) that has smaller particle size than FlorGLO.

# 2. Study objectives

## 2.1. Study objectives

Assess the equivalence of two lutein supplements, FloraGLO and Xanmax on the efficacy of MPOD increase and plasma concentration of lutein in healthy subjects. Assess the improvement of visual functions with the increase of MPOD.

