## 3.4. Number of subjects planned

Thirty-six patients in total (table 1)

Table 1 Number of subjects

|  | | Xanmax | | FlorGLO | | total |
| --- | --- | --- | --- | --- | --- | --- |
|  |  | M | F | M | F |  |
| Young age group | 20-34 yr | 3 | 3 | 3 | 3 | 12 |
| Middle age group | 35-49 yr | 3 | 3 | 3 | 3 | 12 |
| Senile age group | 50-64 yr | 3 | 3 | 3 | 3 | 12 |
| total | | 9 | 9 | 9 | 9 | 36 |

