# 4. Study protocol

## 4.1. Study design

Randomized, double-blind, parallel-group comparison study in a single institute

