4.6. Assignment of the investigational supplement

The assignment personnel will prepare the table to assign the subjects with two supplements, FloraGLO and Xanmax corresponding to the subject number. The number of subjects assigned each supplement has to be equal between men and women. For example, in the group of young men, three men are assigned FloraGLO and three Xanmax.

Table 4. Example of allocation (The actual assignment is different from this)

|  | Investigational  food |  | Investigational  food |
| --- | --- | --- | --- |
| Y-male1 | Xanmax | Y-female1 | FloraGLO |
| Y-male2 | Xanmax | Y-female2 | Xanmax |
| Y-male3 | FloraGLO | Y-female3 | FloraGLO |
| Y-male4 | FloraGLO | Y-female4 | Xanmax |
| Y-male5 | Xanmax | Y-female5 | Xanmax |
| Y-male6 | FloraGLO | Y-female6 | FloraGLO |
|  |  |  |  |
| M-male1 | Xanmax | M-female1 | FloraGLO |
| M-male2 | FloraGLO | M-female2 | Xanmax |
| M-male3 | Xanmax | M-female3 | Xanmax |
| M-male4 | FloraGLO | M-female4 | FloraGLO |
| M-male5 | FloraGLO | M-female5 | FloraGLO |
| M-male6 | Xanmax | M-female6 | Xanmax |
|  |  |  |  |
| S-male1 | Xanmax | S-female1 | FloraGLO |
| S-male2 | Xanmax | S-female2 | Xanmax |
| S-male3 | Xanmax | S-female3 | FloraGLO |
| S-male4 | FloraGLO | S-female4 | Xanmax |
| S-male5 | FloraGLO | S-female5 | FloraGLO |
| S-male6 | FloraGLO | S-female6 | Xanmax |

The assignment personnel will prepare the investigational food according to the allocation table, and send them to the supervisory investigator. The subject number has to be written clearly on each investigational food. Thus, only assignment personnel knows the kind of investigational food assigned to each subject, and the supervisory investigator, investigators, examiners and subjects do not know the kind of investigational food.

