# 9. Evaluation (note; The number is mistaken in the original protocol written in Japanese)

## 9.1. Primary variable

Changes in the macular pigment optical density

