# 17. Anticipated study period

July 1, 2010 to March 31, 2011

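### The protocol aims to show equivalent efficacy in raising MPOD, but has no concurrent control and does not tie the claim to a rise in the FloraGLO arm, so two ineffective arms would satisfy it as often as two equally effective ones

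*Protocol*

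**What the plan says.** - **Objective (Protocol 2.1):** "Assess the equivalence of two lutein supplements, FloraGLO and Xanmax on the efficacy of MPOD increase and plasma concentration of lutein in healthy subjects". The claim is about the efficacy of an increase, not only about similar values.
- **Design (4.1):** "Randomized, double-blind, parallel-group comparison study in a single institute".
- **Arms (4.6):** "The assignment personnel will prepare the table to assign the subjects with two supplements, FloraGLO and Xanmax corresponding to the subject number". No third group appears anywhere. Table 1 in section 3.4 gives 36 subjects, 18 per supplement.
- **Primary variable (9.1):** "Changes in the macular pigment optical density". No section makes a rise in either arm a condition of the conclusion. Section 10 says that a rise is expected, but attaches no consequence if none occurs.
- **Prior evidence (1.1):** in the investigators' earlier studies, which used FloraGLO, MPOD and serum lutein "increased under lutein intake (10 mg/day) in the persons not having AMD but did not in some patients with AMD". No size or variability is given.
- **Schedule (Table 3):** MPOD at baseline and monthly to month 6; blood at baseline, month 3 and month 6. The study period in section 17 is "July 1, 2010 to March 31, 2011".

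**The concern.** In a superiority trial, poor intake, non-response or an insensitive measurement works against the sponsor's claim. In an equivalence trial with two active arms it works in favour of it, because anything that flattens both arms brings them together. If MPOD moved in neither arm, the difference would be near zero, and the data would support a statement of equivalent efficacy that really meant equally without effect. The usual protection is either a concurrent control or a stated requirement that the reference shows its effect in the same trial. This protocol has neither. At stake is the meaning of a positive result on the main objective.

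**Working it through.** **Inputs from the protocol.** Two active arms (4.6). Subjects: 3 age groups × 2 sexes × 2 supplements × 3 per cell = 36, so 18 per arm; Table 1 adds up. The protocol gives no margin, SD, error level or expected rise, so there is no sample-size calculation to reproduce.

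**Assumptions.** Changes are normal with SD 1 in each arm, so everything is in SD of change. Margins m run from 0.5 to 1.25. Equivalence is declared if the 90% confidence interval for the difference lies within ±m; the 95% interval is shown as an alternative. All 18 per arm are analysed.

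**Step 1: the rule does not see the common rise.** With true changes μ_F and μ_X, the estimated difference has mean μ_X − μ_F and standard error s × √(2/18) = 0.333 s. If μ_X = μ_F, the common value drops out. Simulation confirms it: for m = 1 and a 90% interval, the pass probability is 0.80 whether both arms change by 0, 0.5 or 1 SD; with a 95% interval it is 0.66 in all three cases.

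**Step 2: how often two null arms pass.**

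| Assumed margin (SD) | 90% CI | 95% CI |
|---|---|---|
| 0.5 | 0.02 | 0.001 |
| 0.75 | 0.42 | 0.20 |
| 1.0 | 0.80 | 0.66 |
| 1.25 | 0.96 | 0.91 |

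These are also the probabilities of success for two equally effective arms. Even with an observed difference of exactly zero and an observed SD of 1, the margin must exceed 1.691 × 0.333 = 0.56 SD (90% interval) or 2.032 × 0.333 = 0.68 SD (95% interval) for the trial to pass.

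**Step 3: add the condition on FloraGLO.** Require the lower 95% limit of the FloraGLO mean change to be above zero, that is mean > 2.110 × s/√18 = 0.50 s. A true null arm meets this with probability 0.025. With no true rise and a 90% interval, the chance of claiming equivalence becomes 0.003 (m = 0.75), 0.011 (m = 1.0) and 0.019 (m = 1.25).

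**Step 4: what the condition costs when both supplements work equally** (m = 1, 90% interval).

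| True rise in both arms (SD) | FloraGLO condition met | Equivalence, no condition | Equivalence, with condition |
|---|---|---|---|
| 1.0 | 0.98 | 0.80 | 0.80 |
| 0.70 | 0.80 | 0.80 | 0.67 |
| 0.5 | 0.52 | 0.80 | 0.42 |

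**Step 5: what a before-after rise can show.** If section 17 spans first enrolment to last visit, six months of intake within 1 July to 31 March puts baselines in July–September and month-6 visits in January–March. Season is then fully confounded with time on supplement in both arms.

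**The case against.** **The reference is already known to work here.** Section 1.1 reports a rise with FloraGLO in persons without AMD, and this trial enrols healthy volunteers at the same 10 mg of lutein per day. This stands as historical support and makes two null arms less likely. It gives no size, and it cannot show that this trial's intake and measurements were good enough to reveal a rise. A reader might infer from section 1.1 that 10 mg/day fails in people like those enrolled. The text does not support that: the non-responders were some patients with AMD.

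**The real gap is the margin.** A reader might infer from 0.80 and 0.96 that null arms would usually pass under any reasonable margin. That does not follow. Those figures need margins of 1 SD or more, and a margin as large as the reference effect would be hard to defend; at 0.5 SD the figure is 0.02. But at 0.5 SD two equally effective arms also pass with probability only 0.02. At any margin that gives this trial a fair chance of success, null arms share that chance.

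**The decision rule belongs in the SAP.** The condition may be written there, and the SAP is not shown. What this protocol does fix is the absence of a control and a claim worded as efficacy.

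**There are safeguards already.** These are a daily standard-device check and three readings per eye (4.3), discontinuation of subjects who do not take the food as instructed (5.2), exclusion of absorption disorders and earlier lutein use (3.2), and monthly MPOD. They reduce the risk, and two flat arms would be visible. None makes the conclusion depend on what is seen.

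**A before-after test is not a control.** This stands. Requiring a plasma rise as well would not cure it: lutein comes from the diet, so plasma may also vary with season, and a plasma rise does not show that the Raman device can detect a change in MPOD.

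**Conclusion.** The point holds in limited form. The protocol sets an equivalence claim about MPOD increase with two active arms and no concurrent control, and does not tie the claim to a rise in the FloraGLO arm. Two arms without effect therefore satisfy it as often as two equally effective arms. That equality follows from the design and needs no assumed margin. The probability itself does: 0.02 to 0.96 over margins of 0.5 to 1.25 SD with a 90% interval, assuming normal changes and 18 analysed per arm. The documents do not show that two null arms are likely, and the earlier FloraGLO findings point the other way. Nor does the lack of an untreated arm make the trial uninformative: it still compares the supplements fairly, and only the word efficacy lacks support from within the trial. This should be changed; it does not invalidate the trial.

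**What to change.** Add one sentence to sections 2.1 and 9.1: equivalent efficacy on MPOD increase is concluded only if, besides the between-arm criterion, the lower 95% confidence limit of the mean month-6 MPOD change from baseline in the FloraGLO arm is above zero. Report the plasma lutein change alongside as supporting evidence of intake, not as a second condition. If the condition fails, report the difference with its confidence interval; the arms may be described as not different, but without a claim of equivalent efficacy.

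The change uses measurements already scheduled and needs no further subjects or visits. Its cost is the loss of probability of claiming equivalence shown in Step 4, which depends on a true rise that the protocol does not give. It is also only a partial repair: without a concurrent control, a before-after rise cannot be separated from season or drift, and the report should say so.

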3.2. Inclusion criteria

No ocular pathologies detected by slit-lamp biomicroscopy and fundus ophthalmoscopy

Visual acuity of 0.8 or better at the time of the MPOD measurement

A spherical equivalent refractive error of less than -6.0 dioptor

No gastrointestinal diseases that could cause disturbance of dietary absorption

No diabetes

No history of lutein supplementation

No allergy to lutein and zeaxanthin

No history of smoking at least within one year

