# 4.7. Investigational food

1. Xanmax lutein:

One capsule contains 10 mg of lutein and 1mg of zeaxanthin. Suspension is safflower oil.

1. FloraGLO lutein (DSM Co.Ltd):

One capsule contains 10 mg of lutein and 0.05mg of zeaxanthin. Suspension is corn oil.

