### 9.2. Secondary variables

1. Changes in the far and near visual acuity
2. Changes in the contrast and glare sensitivity
3. Change in macular ERG
4. Changes in the plasma lutein level

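### The visual-function objective speaks of improvement, but with both arms on lutein, one baseline and no untreated comparison the trial can support only an exploratory association with MPOD change

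*Protocol*

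**What the plan says.** Protocol section 2.1 sets two objectives. The first is product against product: "Assess the equivalence of two lutein supplements, FloraGLO and Xanmax on the efficacy of MPOD increase and plasma concentration of lutein in healthy subjects". The second is of another kind: "Assess the improvement of visual functions with the increase of MPOD".

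The design in section 4.1 is a "Randomized, double-blind, parallel-group comparison study in a single institute". Section 4.6 has the assignment personnel "assign the subjects with two supplements, FloraGLO and Xanmax corresponding to the subject number", and no other assignment exists. Section 4.7 gives the contents: for Xanmax, "One capsule contains 10 mg of lutein and 1mg of zeaxanthin"; for FloraGLO, "One capsule contains 10 mg of lutein and 0.05mg of zeaxanthin". Every subject takes one capsule a day (section 4.8) for six months (section 4.9).

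Table 3 shows one pre-intake assessment, with intake from the following day. Acuity and contrast/glare are tested at enrolment, 3 and 6 months, and macular ERG at enrolment and 6 months. Section 9.2 lists the visual functions only as changes, for example "Changes in the contrast and glare sensitivity". Nothing there links them to the change in MPOD.

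**The concern.** Randomisation here separates two lutein products. It does not separate lutein from no lutein, or raised MPOD from unchanged MPOD. Section 10 expects MPOD to rise with lutein intake, so a rise is anticipated in both arms.

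Anything else that moves visual-function scores between enrolment and six months is then mixed into the before-after change. Acuity and contrast/glare are scored on the subject's responses, so familiarity with the test and expectation can shift them. The blinding in section 4.6 hides which product is taken, and both products are lutein. Time may matter too. If the period in section 17 (July 2010 to March 2011, nine months) runs from first enrolment to last visit, baselines fall in July to September and six-month visits in January to March, in both arms. No second pre-intake test is scheduled from which a retest gain could be estimated.

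The risk is a report that MPOD rose and vision improved, read as a benefit of lutein, when the two changes merely happened over the same six months. Section 1.1 itself notes that some studies found no such benefit, so it cannot be taken for granted.

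**Working it through.** **The plan's own figure.** The protocol gives a sample size but no power calculation. Table 1 in section 3.4 reproduces: 3 age bands × 2 sexes × 2 products × 3 subjects = 36, or 18 per arm.

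**Assumption.** The documents give no retest or time effect. A range of 0 to 0.5 SD of the change score is used, with the true lutein effect set to zero.

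**1. Before-after test.** For a one-sample t test on change, the statistic follows a noncentral t distribution with n − 1 degrees of freedom and noncentrality d√n. With n = 36, √n = 6, so d = 0.3 gives 1.8 and d = 0.5 gives 3.0. The probability of a significant result at two-sided 5% is:

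| Shift (SD of change) | All 36 subjects | One arm, 18 subjects |
|---|---|---|
| 0 | 0.05 | 0.05 |
| 0.1 | 0.09 | 0.07 |
| 0.2 | 0.22 | 0.13 |
| 0.3 | 0.42 | 0.23 |
| 0.4 | 0.65 | 0.36 |
| 0.5 | 0.83 | 0.52 |

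These figures count both directions. In the direction of improvement alone, the n = 36 values are 0.025 at no shift and 0.084 at 0.1 SD. From 0.2 SD upward the difference is 0.001 or less.

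**2. What a common shift does to other analyses.** In 20,000 simulated trials of 36 subjects, mean MPOD change was 0.5 SD, the pure retest gain in function was 0.4 SD, and the two were unrelated. Share of trials significant at 5%:

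- before-after change in function: 65%
- before-after rise in MPOD: 83%
- both together: 54%
- correlation of change in function with change in MPOD: 5.2%
- difference in function between randomised products: 5.0%

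The last two stay near their nominal level, while the before-after reading does not.

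**3. What those two analyses can detect.**

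- Correlation, by Fisher's z at 80% power: r = tanh[(1.96 + 0.84)/√(36 − 3)] = tanh(2.80/5.74) ≈ 0.45.
- Between-product difference, 18 per arm, at 80% power: (1.96 + 0.84) × √(2/18) = 2.80 × 0.333 ≈ 0.93 SD of change.

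**The case against.** The strongest reply is that no section prescribes a before-after test. Section 9.2 names variables, and the section 2.1 wording can be read as an association between functional change and MPOD change, which a common retest shift does not bias. A statistical analysis plan, not among the documents reviewed, could specify exactly that. This stands in part: a false claim of improvement is a risk, not something the protocol commits to. But the arms, the visit schedule and the objective are fixed in the protocol. No analysis plan can supply an untreated comparison, and an association does not justify the word improvement.

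Three further inferences are tempting but unsupported.

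- *The randomised comparison is silent on this objective.* It is not. Section 1.1 describes a smaller particle size for Xanmax, and section 4.7 shows different zeaxanthin contents (1 mg against 0.05 mg), so MPOD gain may differ by product. A matching difference in function would be randomised evidence, though weak at this sample size.
- *The entry limit leaves no room for acuity to improve.* Section 3.2 requires "Visual acuity of 0.8 or better at the time of the MPOD measurement", which is a minimum; no ceiling or baseline distribution is given. A ceiling would also limit a spurious practice gain, so the argument cuts both ways.
- *Practice and expectation distort every function alike.* Macular ERG is an electrophysiological recording, not an effort-scored response, so those arguments do not carry over directly. It still has no control for time.

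**Conclusion.** The point holds as a limit on what may be claimed. Before-after change in visual function cannot be attributed to lutein or to raised MPOD in this design, and the randomised contrast helps only through a between-product difference in MPOD gain.

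The lack of control is documented; the size of the resulting error is not. Under the assumed range, the rate of significant before-after change with no lutein effect runs from the nominal 0.05 to 0.83 with all 36 subjects. If retest effects are near zero, the practical harm is small.

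A reader might infer that the objective is unanswerable or that the trial is compromised. The documents support neither. An association between changes can be explored with data already scheduled. The primary variable, change in MPOD, and the randomised product comparison are untouched. This is a worthwhile correction to a secondary objective.

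**What to change.** 1. Restate the second objective in section 2.1 as: *Explore whether subjects with larger MPOD increase show larger change in visual function.*
2. Analyse it by regressing the 6-month change in each function on the 6-month change in MPOD, adjusted for baseline function, sex and age group. Fit it with and without arm, because adjusting for arm removes the part of MPOD variation that randomisation created.
3. Report the randomised between-product difference in each function alongside.
4. Label the result exploratory and associational. A common retest shift falls in the intercept only if it is unrelated to MPOD change; adherence, motivation or diet could link the two. State also that 36 subjects give 80% power only for r of about 0.45.
5. State that pre-post change alone will not be reported as an effect of lutein or of MPOD.

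The cost is a change of protocol wording and two regression fits per function, with no added arm, visit or subject. The claim becomes weaker, and a null association will be uninformative unless the true correlation is fairly large.
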